### Sample Size Calculation

This study was based on a clinical trial of a Chinese herbal medicine compound KDGs, for the treatment of HT. The study followed a randomized, double-blind, placebo-controlled design, with a change in the TPOAb level after 12 weeks of treatment serving as the primary efficacy endpoint. Using a 1:1 allocation ratio, the study participants were randomly assigned to either the TCM (KDGs) or the placebo group (placebo granules).

To determine the sample size, we used a clinical study sample size calculation formula:

[figure not shown]

Considering the mean change in TPOAb levels before and after treatment in the treatment group (μ1=120, SD σ1=200) and the control group (μ2=20, SD σ2=200) based on previous study results [17], the study aimed to achieve a power of 80% (1 - β=.80), with a significance level of 0.05 (two-sided) and a β of .20. The calculated sample size was 64, and with a 10% dropout rate, 140 participants were required for the study, with 70 individuals in each group.

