### Evaluation

#### Primary Outcome

Difference in TPOAb levels before and after treatment.

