#### Fundamental Principles

In this study, all statistical inferences were made using a 2-sided test at a significance level of α=.05. The confidence intervals of the study parameters were estimated using 2-sided 95% CIs to indicate the statistical significance of differences.

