#### Handling Missing Data and Sensitivity Analysis Plan for Missing Data

Missing data will be handled using Multiple Imputation under the assumption of Missing at Random. Multiple (eg, m=20) complete datasets will be generated by imputing missing values using a multivariate model incorporating key baseline and outcome variables. The planned primary and secondary analyses will be performed separately on each imputed dataset. Final estimates (eg, treatment effects, confidence intervals, and *P* values) will be obtained by pooling the results from all m datasets using Rubin rules. A sensitivity analysis assuming a Missing Not at Random scenario will be conducted to assess the robustness of the conclusions. Safety evaluations were not performed for missing data.

To ensure the robustness of the conclusions from the primary analysis, the following prespecified sensitivity analyses will be performed regarding missing data. First, the results from the primary analysis using multiple imputation will be compared with the results from an analysis based on the complete-case dataset. Second, a worst-case scenario analysis will be conducted. This analysis will assume that all participants in the intervention group with missing primary outcome data experienced treatment failure (eg, no symptomatic improvement or no reduction in antibodies), while all participants with missing data in the control group experienced treatment success. The primary outcome will be re-evaluated under this extreme assumption. These sensitivity analyses aim to assess whether the study conclusions are sensitive to the methods used for handling missing data. Consistency between the results of these analyses and the primary analysis would provide stronger support for the reliability of the final conclusions.

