#### Inferential Statistics

Baseline data, efficacy indicators, and safety indicators underwent inferential statistical analysis. Baseline data: statistical inferential analysis was conducted based on the type of variable to compare the comparability of the participants in the experimental and control groups. Quantitative variables were analyzed using 2-tailed *t* tests for normally distributed data and nonparametric rank-sum tests for nonnormal distribution. Qualitative variables were analyzed using chi-square tests. Efficacy indicators: comparative analysis of quantitative variables within groups was conducted using paired *t* tests for normally distributed data and paired nonparametric rank-sum tests for nonnormal distribution. Differences in efficacy indicators before and after the intervention were calculated separately for the experimental and control groups, and *t* tests or rank-sum tests were used to assess the statistical significance of these differences. Analysis of covariance, which considers the center effect, was used to provide the mean (or adjusted mean), difference in means, and 95% CIs for each group. Paired chi-square tests were used for qualitative variables, and the Wilcoxon rank-sum test was used for ranked variables. If the baseline comparability of the experimental and control groups was poor, general linear models and logistic regression models were applied for adjustment. Safety analysis: the chi-square test was used to compare the incidence of adverse events between the 2 groups, and a list was used to describe the adverse events that occurred in the trial. Intergroup and intragroup comparisons of quantitative indicators were performed using the corresponding differential tests. Laboratory test results were analyzed for changes in normal/abnormal values before and after the study, and a list was provided for abnormal values.

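### The primary TPOAb change has several parallel analyses with none named as primary, and baseline adjustment is stated only as conditional on observed imbalance

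*Protocol article*

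**What the plan says.** All references are to the protocol article.

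- **Endpoint.** Sample Size Calculation sizes the trial "with a change in the TPOAb level after 12 weeks of treatment serving as the primary efficacy endpoint". Primary Outcome defines it as "Difference in TPOAb levels before and after treatment" and attaches no model.
- **Tests.** Inferential Statistics covers all efficacy indicators together. For the before/after differences, t tests or "rank-sum tests were used to assess the statistical significance of these differences".
- **Estimates.** The same section adds: "Analysis of covariance, which considers the center effect, was used to provide the mean (or adjusted mean), difference in means, and 95% CIs". Centre is the only term named.
- **Conditional adjustment.** "If the baseline comparability of the experimental and control groups was poor, general linear models and logistic regression models were applied for adjustment". The section gives no threshold for poor comparability and lists no covariates. Baseline data are compared between arms by inferential tests.
- **Decision rule.** Under Fundamental Principles, "all statistical inferences were made using a 2-sided test at a significance level of α=.05", and parameters are "estimated using 2-sided 95% CIs to indicate the statistical significance of differences".
- **Missing data.** The planned primary analysis is run on each imputed dataset (m=20 is given as an example), and treatment effects, intervals and P values "will be obtained by pooling the results from all m datasets using Rubin rules". Which analysis is the primary one is not said.
- **Data available.** Table 1 under Study Design schedules TPOAb at baseline and at week 12 for every participant.

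**The concern.** One powered question has three routes to an answer, and the text does not rank them. Three things follow.

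1. **Two decision rules.** Since intervals indicate significance, the ANCOVA interval is a second verdict beside the t or rank-sum P value. The two can disagree, and the plan does not say which one counts.
2. **A weak link to the imputation plan.** Rubin's rules combine an estimate and its standard error. A rank-sum test supplies neither. If the choice of test follows a normality check, that check can also come out differently in different imputed datasets.
3. **Adjustment triggered by the data.** Using baseline only after an imbalance is seen makes the model depend on the data, and in most trials it forgoes precision from a measurement already taken. If the trigger is a baseline test at 5%, about 95% of trials would not receive this adjustment.

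The interpretation of the main result and some of its power are at stake.

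**Working it through.** **Inputs from the protocol article.** Mean change 120 (KDGs) and 20 (placebo), SD 200 in each arm, two-sided α=.05, power 80%, 1:1 allocation, 10% dropout, 70 per arm; three centres with 80, 30 and 30 participants.

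**Assumed, because not in the document.** The correlation r between baseline and week-12 TPOAb (0.5, 0.7, 0.9), equal SDs at the two times, and the shape of the TPOAb distribution in the simulations.

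**Step 1: the plan's own figure.** Normal approximation: n = 2(1.960+0.842)² × 200²/100² = 62.8 per arm. Two-sample t test: 63.8, so 64 per arm, as stated. The size therefore matches an unadjusted comparison of mean change. With 70 per arm and 10% dropout, 70 × 0.9 = 63 are evaluable, and t-test power is 79.5%.

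**Step 2: effect of always adjusting for baseline.** Let s be the SD at each time.
- Variance of change: 2s²(1−r).
- Residual variance after regression on baseline: s²(1−r²).
- Ratio: (1−r²)/[2(1−r)] = (1+r)/2.

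Hold the change SD at 200, so the effective SD is 200√[(1+r)/2]:

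| r | Variance ratio | Effective SD | Power at 63 per arm | n per arm for 80% (normal approx.) |
|---|---|---|---|---|
| unadjusted | 1 | 200 | 79.5% | 63 |
| 0.5 | 0.75 | 173.2 | 89.5% | 48 |
| 0.7 | 0.85 | 184.4 | 85.5% | 54 |
| 0.9 | 0.95 | 194.9 | 81.5% | 60 |

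Power uses the two-sample t test and ignores the few degrees of freedom spent on baseline and centre. The gain shrinks as r approaches 1.

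**Step 3: type I error.** Simulation under no effect: 63 per arm, centres in proportion 80:30:30, 8000 trials per scenario, r from 0.5 to 0.9. The test was chosen by a Shapiro–Wilk check at 5%, and imbalance was declared at baseline P<.05. TPOAb was normal or log-normal (log-SD 0.8).

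| Reported result | Normal | Log-normal |
|---|---|---|
| Better of the chosen test and centre-only ANCOVA | 5.7–6.0% | 6.7–7.2% |
| Same, plus the baseline model when triggered | 5.8–6.1% | 6.9–7.4% |
| Same, with the baseline model always available | 7.0–8.1% | 8.2–9.1% |

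Following the rule literally (one test, replaced by the baseline model only when triggered) gave about 4–6% in separate runs. Any one of the analyses fixed in advance stays near 5%. The chosen test and the baseline-adjusted model disagreed on significance in about 3–6% of null trials.

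**The case against.** The strongest reply is that a condensed article may leave the ordering of models to the analysis plan, and that the text is less bad than it looks. Much of the detail stands.

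- **Baseline is not ignored.** A reader might infer that baseline TPOAb enters only when the arms look unbalanced. The endpoint is a before/after difference, so baseline is already subtracted. The ANCOVA is unconditional and its continuous covariate is unstated, so it could be baseline. What can be said is that baseline is not named as a covariate and that baseline adjustment is stated only as conditional.
- **The normality gate is inferred.** The condition is explicit for baseline comparisons and within-group paired tests. For the between-group change the text only offers the two tests as alternatives.
- **The ANCOVA is not described as giving a P value.** It competes only because intervals are used to indicate significance.
- **Error inflation is modest.** Counting a trial as positive when any of the t test, rank-sum test, centre-only ANCOVA or baseline-adjusted model reaches P<.05 gives 8.5–9.9% under skewed assumptions. That figure needs the baseline model to be available in every trial, which the stated rule does not allow.
- **The Rubin conflict is partial.** It arises only if the rank-sum test is the pooled primary result; ANCOVA estimates pool normally.
- **A log-scale primary analysis is not compelled.** In one assumed setting (log-normal, log-SD 1.0, true 33% reduction; r=0.5, 0.7, 0.9), log-scale baseline ANCOVA has 72%, 87% and about 100% power, against 30%, 42% and 80% for centre-only ANCOVA. The rank-sum test, which such skewed data would usually select, has about 46%, 65% and 97%. The multiplicative effect favours the log model, and the article gives no TPOAb distribution.

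The appeal to an analysis plan does not remove the point. The article does not merely omit a model: it states parallel analyses and a data-dependent adjustment rule. An analysis plan that followed this text would inherit both.

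**Conclusion.** The point holds in a limited form. The article names no primary analysis among those it lists for the TPOAb change, states baseline adjustment only as conditional on undefined imbalance, and allows an interval and a P value from different analyses to conflict. I rate it as something the sponsor should fix, not as a flaw that invalidates the trial.

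The main cost is precision: 2 to 10 percentage points of power at 63 per arm for r between 0.9 and 0.5, given equal SDs at the two times and a change SD of 200. If the unstated ANCOVA covariate is in fact baseline, that gain is already available from the ANCOVA, and what remains is to say so and make it primary. Type I error is near 5% under the literal rule and about 6–9% under selective reporting, on assumed distributions. A reader might infer a serious loss of error control or a wrong sample size; neither is supported, and the sample size reproduces.

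**What to change.** Before unblinding, in a dated amendment or analysis plan:

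1. Name one primary analysis: ANCOVA of TPOAb change on treatment, baseline TPOAb and centre. With baseline in the model, using week-12 TPOAb as the response gives the same treatment effect.
2. Take the estimate, 95% CI and P value from that model, pooled by Rubin's rules.
3. Delete the clause that makes adjustment depend on observed imbalance, and any data-driven choice of test for the primary endpoint.
4. Keep the rank-sum test and a log-scale baseline-adjusted ANCOVA as labelled sensitivity analyses.

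This keeps the stated absolute-difference endpoint on which the trial was sized. Making a geometric mean ratio primary would replace that endpoint. It would also need a rule for very low values, since Participant Screening and Selection admits patients positive for either antibody and so some may be TPOAb-negative.

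The cost is wording only: no new data and no more participants. Timing matters. The Abstract says the data have not yet been analysed, while the Results section says analysis is under way, so the amendment should state the actual position and confirm that the choice was made blind to allocation.

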### Clinical Trial End

The trial will end once 140 participants have been recruited, and all participants have completed 12 weeks of treatment and 12 weeks of follow-up.

### Ethical Considerations

The research protocol and informed consent form received approval from the Clinical Research Ethics Committee of Yueyang Hospital of Integrated Traditional Chinese and Western Medicine, affiliated with Shanghai University of Traditional Chinese Medicine, on December 14, 2022 (Approval No 2022-123). Before participating in the research, we will obtain written informed consent from all participants. We will ensure voluntary participation and maximum confidentiality of the information provided during the interviews. The trial will be supervised by the Ethics Committee. Any moderate or severe adverse reactions will be reported to the Ethics Committee. Participants who experience adverse reactions during the trial will receive free access to medical care.

All research-related information will be securely stored at the research site, and all participant information will be stored in a locked filing cabinet with restricted access. To ensure participant confidentiality, all laboratory samples, reports, data collection, processes, and management forms will be identified using coded ID numbers. All records containing names or other personal information (such as informed consent forms) will be stored separately from the coded research records. All local databases will be protected using password-protected access systems. Forms, lists, logs, appointment books, and other lists linking participant identification to other identifying information will be stored in restricted access areas in individually locked files.

The relevance and necessity of the research questions, research design, and patient-centered documents (including informed consent forms, participant information sheets, symptom diaries, all follow-up forms, and promotional materials) have been subjected to review by the public. The public engagement group comprised individuals with experienced and inexperienced backgrounds. Efforts will be made to collaborate with patient advocacy groups to ensure that easily comprehensible abstracts of research findings are shared with participants and the broader patient community. The intervention burden will be comprehensively and reasonably assessed through communication between participants and researchers. While the results will not be communicated directly to the participants, the final outcomes will be disseminated. Throughout the follow-up period, all the examination results will be communicated to each participant.

All study data, including source documents, CRFs, and electronic databases, will be retained by the Sponsor for a period of at least 5 years after the completion or termination of the study. Upon expiration of the retention period, electronic data will be permanently deleted using irreversible methods, and paper records will be confidentially destroyed and incinerated. A certificate of disposal will be issued and maintained in the study files.

Blood samples collected during the study will be stored under coded identifiers at Yueyang Hospital of Integrated Traditional Chinese and Western Medicine, affiliated with Shanghai University of Traditional Chinese Medicine. For specimens authorized for future research, as permitted by the informed consent form, these specimens will be retained indefinitely in a secured biobank for use in future research projects. Any future use will be subject to approval by a Research Ethics Board. When selecting eligible participants, researchers must provide detailed information about the clinical trial, including the purpose of the trial, trial procedures, potential benefits and risks, and the rights and responsibilities of participants, so that participants can fully understand and have sufficient time to consider. After the participants’ questions have been answered satisfactorily, they will sign informed consent forms and receive the physician’s contact details so that they can contact the physician at any time if there are any changes in their condition.

### Randomization

After screening, SAS software was used to generate random numbers, and a sequential randomization plan was used to allocate the study participants to the experimental and control groups to ensure group balance. The investigator sequentially assigned a drug number to each participant based on the enrollment order and dispensed the corresponding test drug number that could not be selected arbitrarily. The number of assigned drugs remained constant throughout the study.

## Results

Participant recruitment commenced in June 2023. All intervention and concurrent data collection activities are scheduled for completion by May 2025, with the 12-week follow-up assessment postintervention expected to conclude by the end of May 2025. Data management has been finalized, and data analysis is presently in progress. For data inquiries, kindly reach out to the primary author. The conclusive outcomes of the research will be disseminated in a journal indexed in the Science Citation Index. The study protocol is illustrated in Figure 1.

**Figure 1 figure1:**
[figure not shown]
Flow chart of the study procedure. HT: Hashimoto thyroiditis; KDGs: kangjia decoction granules; TCM: traditional Chinese medicine;.

## Discussion

### Principal Findings

This study anticipates that the KDGs can effectively reduce TPOAb and TGAb levels in patients with HT of the liver depression and spleen deficiency pattern, without significant adverse reactions. It is also expected to ameliorate patients’ clinical symptoms and signs, thereby improving their quality of life. Furthermore, KDGs may decrease the expression of *IL17* mRNA and increase the expression of *FOXP3* mRNA in patient serum, helping to improve the immune microenvironment and regulate immune balance.

During the progression of HT, aberrant immune responses and dysregulated recognition processes modulate the induction of apoptosis, leading to increased follicular cell death, irreversible fibrosis of the follicular architecture, and diminished capacity for thyroid hormone synthesis, ultimately resulting in hypothyroidism. Consequently, most patients require lifelong thyroid hormone replacement. Even with normalized thyroid hormone levels, patients often experience symptoms such as fatigue, lower limb edema, depression, and anxiety, which severely impact their quality of life. In conventional Western medicine, the primary treatment for HT relies on levothyroxine replacement to correct thyroid dysfunction. However, this approach lacks effective intervention for the early-stage immune imbalance in HT and shows limited efficacy in reducing autoantibodies (TPOAb and TGAb). Traditional Chinese Medicine identifies “liver depression and spleen deficiency” as a core pathogenesis of HT. Previous clinical observations and studies have demonstrated the efficacy of the KDGs granules in ameliorating HT symptoms and reducing autoantibody levels. KDGs is known for its properties of soothing the liver, strengthening the spleen, clearing heat, and dispersing stagnation. Animal studies have further validated its potential to lower TPOAb and TGAb levels and enhance thyroid function in model rats.

Although numerous clinical studies on Chinese medicine exist, there is a general lack of high-quality, large-sample, randomized, double-blind controlled trials. To address these gaps, this study adopts a “disease-pattern integrated” model, focusing on the core TCM pattern of “liver depression and spleen deficiency,” and uses a fixed herbal formula for intervention. Through a rigorous randomized, double-blind, controlled trial design, it aims to provide high-level evidence for TCM pattern-based treatment. Regarding efficacy evaluation, most existing studies primarily focus on changes in thyroid function and antibody titers, with insufficient exploration of the underlying mechanisms of immune imbalance [21-23]. This study innovatively incorporates key markers of Th17/Treg cell balance—the proinflammatory cytokine IL-17 and the transcription factor FOXP3—as core outcome measures. This allows for an in-depth investigation of the drug’s potential immunomodulatory targets, effectively complementing traditional evaluation models. In terms of study design, addressing limitations such as small sample sizes and lack of blinding in some previous herbal medicine research, this study uses a multicenter, randomized, double-blind, controlled trial design to minimize bias and enhance the reliability and generalizability of the findings.

This study protocol possesses several notable strengths. First, it provides a novel theoretical integration of the TCM principle of “soothing the liver and strengthening the spleen” with contemporary immunoregulatory theory. The pathophysiology of HT involves a dysregulated neuro-endocrine–immune network that manifests in systemic symptoms, a concept well-aligned with the TCM framework. We propose a mechanistic correspondence: “Liver depression” may correlate with stress-axis (hypothalamic-pituitary-adrenal axis) dysfunction and neurotransmitter disturbances underlying depression and anxiety, while “spleen deficiency” may relate to gut-barrier dysfunction, metabolic dysregulation, and inflammation-induced sarcopenia, reflecting the TCM concept of the “spleen governing the muscles.” The therapeutic principle of soothing the liver and strengthening the spleen thus represents a multitarget, systems-level intervention aimed at restoring immune-neuro–metabolic homeostasis. This integrative model offers a coherent pathophysiological rationale for targeting the co-occurrence of emotional, cognitive, and muscular symptoms in HT, underscoring the holistic perspective of TCM and providing a scientific foundation for the study hypothesis.

Second, the selection of outcome measures is comprehensive and mechanistically informed.​ Beyond assessing conventional HT biomarkers (TPOAb and TGAb), the protocol includes key mediators of the Th17/Treg pathway (*IL17* and *FOXP3* mRNA expression). This dual approach allows for a systematic evaluation​ of the intervention’s effects on both downstream autoantibody production and upstream immunologic imbalance, offering deeper insights into its potential mechanism of action.

Third, the methodology is robust. Using a multicenter, randomized, double-blind, placebo-controlled design​ minimizes bias, enhances generalizability, and is conducive to generating high-level clinical evidence, which addresses a common limitation in prior TCM interventional research.

Finally, the study addresses a clear unmet clinical need. It directly targets the persistent challenge of reducing thyroid autoantibodies and modulating the underlying immune dysregulation in HT, a gap in current conventional management. Positive results could offer a novel adjunctive strategy aimed at modifying the immune microenvironment and improving patient outcomes.

However, this study also has several limitations. First, Chinese herbal formulas are characterized by multiple components and targets. The specific active material basis of KDGs and its detailed mechanisms of action cannot be fully elucidated merely through changes in clinical indicators. Moreover, although the TCM pattern diagnosis of “liver depression and spleen deficiency” can be quantified using scales, a degree of subjectivity remains, which may affect the homogeneity of the enrolled patients regarding their pattern presentation. Second, HT is a chronic disease requiring a prolonged period for immune modulation. This study’s duration may be insufficient to fully evaluate the long-term efficacy of the intervention, the stability of antibody levels over time, and its long-term impact on disease progression (eg, changes in thyroid volume and incidence of clinical hypothyroidism). Finally, the inference of immunological changes in this study is primarily based on the detection of cytokines and transcription factors in peripheral blood, which constitutes indirect evidence. It cannot directly reflect the immune cell infiltration and inflammatory microenvironment within the thyroid gland itself, thereby limiting the depth of mechanistic interpretation.

Based on the positioning and potential findings of this study, future research directions may include, at the mechanistic level, further studies that could use flow cytometry to directly analyze the proportions of Th17 and Treg cells in patient peripheral blood. Using animal or cell models, research could delve deeper into the regulatory effects of KDGs and its active components on key signaling pathways related to Th17/Treg cell differentiation and function, such as RORγt, STAT3, and TGF-β/Smad. Furthermore, research dimensions should be expanded, for instance, by conducting long-term follow-up studies to assess the intervention’s long-term benefit in delaying progression to clinical hypothyroidism.

To facilitate translation, should the positive outcomes of this trial be confirmed, future studies could validate its efficacy and safety in real-world clinical settings. Research could also explore its synergistic effects when combined with Western medications (eg, selenium yeast and levothyroxine), aiming to establish a comprehensive management pathway for HT integrating TCM and Western medicine characteristics.

